#### Definition of time 0 and the index visit

Time 0 is defined as the time at which individuals meet the eligibility criteria and ‘enter’ the emulated trial, analogous to the time of randomisation in the target trial. Time 1 is 12 months postbaseline, and the outcome of interest is forced expiratory volume in 1 s (FEV_1_%) at time 1.

For the emulated trials conducted within period p (p=1,2,3), we define an ‘index visit’ for each individual who meets the eligibility criteria during the recruitment period, such that the date of the index visit is time 0. Follow-up visits take place approximately 12 months after the index visit, and an eligibility criterion is that individuals are required to have a follow-up visit. Index visits and follow-up visits are defined differently in the UK and US emulated trials, due to differences in data collection between the two registries. Moreover, the visit we use for treatment, outcome and covariate data at time 0 and time 1 differs between the UK and US emulated trials; figure 1 summarises these differences.

**Figure 1 F1:**
[figure not shown]
Study design diagram illustrating from which visits data are extracted for time 0 and time one in the UK and US Emulated Trials. Subscripts denote time. FEV_1_, forced expiratory volume in 1 s.

##### UK CF Registry Data

Using annual review data only

Within the period p, the index visit for a given individual is the first annual review visit at which they meet the eligibility criteria in the 2-year recruitment period. The follow-up visit is the date of the next annual review which is closest to 12 months after time 0, but falls within 9–15 months after time 0. The outcome is FEV_1_% measured on the day of the follow-up visit. Individuals are included in the treated group if they are recorded as being prescribed azithromycin at the follow-up visit because the information recorded on treatment use at the annual review refers to treatment use over the past year. Individuals not recorded as being prescribed azithromycin at the follow-up visit are included in the control group.

Using annual review data and prescription dates data

In the UK Registry, prescription dates data are available from 2016 onwards. Therefore, in period 3 (2016–2018), we can conduct a second analysis making use of the dates data for a more precise time 0. In the second analysis, the index and follow-up visits are defined as above for individuals in the control group. For treated individuals, the index visit is defined similarly; however, time 0 is defined as the first date post-index visit at which azithromycin is prescribed. The follow-up visit is defined as the next annual review visit which is closest to 12 months after time 0, but falls within 9–15 months after time 0.

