Eligibility criteria	Include: French individuals diagnosed with CF (sweat chloride >60 mmol/L or a genotype known to cause the disease), aged 6–21 years, with the ability to perform pulmonary function tests with FEV_1_%>40 and the ability to swallow tablets.Individuals were excluded if they had the following: Allergy to macrolide antibiotics Long-term (>3 months) with macrolides during the 12-month period before study entry Liver disease with liver function tests >2 times the laboratory upper limit History of portal hypertension Kidney disease with serum creatinine >150 µmol/L and/or creatinine clearance <50 mL/min Use of any of the following in the 3 months before study entry: DNase, inhaled tobramycin, inhaled steroids	Individuals will be considered for inclusion if they have a clinically confirmed diagnosis of CF (ie, are present in the UK CF Registry) and have an observation date within the recruitment periods defined in section 4.3.1, aged between 6 and 21 years, and obtained FEV_1_%>40 on their pulmonary function test (taken on the day of the annual review). It is assumed that all individuals have the ability to swallow tablets.Exclusion criteria are as follows: Intolerance to macrolide antibiotics recorded at any time during study period. Prescription of chronic oral or prophylactic oral macrolides (including azithromycin) recorded at time 0. Acute liver failure with >3×the upper laboratory limit, INR>2, or not responsive to vitamin K at time 0 Recorded cirrhosis with portal hypertension at time 0. Serum creatinine levels >150 µmol/L at time 0. Prescription of DNase, inhaled tobramycin or inhaled corticosteroids recorded at time 0. No follow-up visit for time 1.	Individuals will be considered for inclusion if they have a clinically confirmed diagnosis of CF (ie, are present in the US CF Registry) and have an observation or encounter date within the time periods defined in section 4.3.1, aged between 6 and 21 years, and obtained FEV_1_%>40 on their pulmonary function test (taken on the day of the encounter visit). It is assumed that all individuals have the ability to swallow tablets.Exclusion criteria are as follows: As in the UK Emulated Trial As in the UK Emulated Trial Non--related liver disease recorded at time 0. Laboratory results from liver tests are not available in the US registry. Recorded cirrhosis at time 0. Portal hypertension is not available in the US registry. As in the UK Emulated Trial As in the UK Emulated Trial As in the UK Emulated Trial

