**Figure 2 F2:**
[figure not shown]
Directed acyclic graph depicting assumed confounding relationships for the association between azithromycin at time 0 (azithromycin0) and FEV1% at time 1 (FEV1%1). U represents any unmeasured confounders. Subscripts denote time; 0* indicates prebaseline. BMI, body mass index; CFRD, cystic fibrosis-related diabetes; FEV_1_, forced expiratory volume in 1 s; NTM, nontuberculous mycobacteria; ppFEV_1_, per cent predicted FEV1.

Age, FEV_1_% and BMI z-score are continuous. Rate of decline in FEV_1_% is calculated as the difference between the absolute FEV_1_% measured at the index visit and the prior visit. Data on treatment prescription, the presence of infections, CFRD diagnosis, pancreatic insufficiency and non-intravenous hospital admissions will be binary indicators. Indicators for pancreatic insufficiency and non-intravenous hospital admissions are created using existing variables in the data. Registry data provide dates for treatment with intravenous antibiotics (at home or hospital). These data will be used to create a variable indicating the number of days on intravenous antibiotics since the last annual review (including treatment administered at home and hospital). Intravenous days will then be treated as a categorical variable with four categories: 0, 1–14, 15–28, 28+.

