#### Main analysis

In the target trial, the authors investigated the change in FEV_1_% from baseline, with adjustment for baseline FEV_1_%. This is equivalent to a regression of the mean FEV_1_% at follow-up with adjustment for baseline FEV_1_%. We note that in the absence of imbalance between treatment groups in baseline FEV_1_%, the adjustment of baseline FEV_1_% is not required but may result in gains in efficiency. Both approaches result in estimates of the ATE as defined in equations(1)  (2).

In the emulated trials, we need to account for differences between treatment groups at baseline, including baseline FEV_1_%. We also require assumptions of positivity, no interference, consistency and conditional exchangeability (conditional on C). We use augmented inverse-probability-of-treatment weighting (AIPTW) to control for potential confounding by C. AIPTW involves defining models for the treatment and outcome. This approach was chosen as it is doubly robust, meaning that it gives consistent estimates of treatment effects if either the treatment model or outcome model is correctly specified.^27^ This represents an advantage compared with the alternative propensity score or outcome-regression based approaches which are singly robust.

The first step in implementing AIPTW is to estimate the propensity scores, that is, the probability of treatment conditional on baseline covariates:

(3)
PS=P(A=1|C)

Propensity scores will be estimated using logistic regression, including C as linear terms.

In the second step, we specify an outcome model conditional on treatment and covariates:

(4)
$$Y_{1}=\gamma_{0}+\gamma_{A}A+\gamma_{C}C+\varepsilon$$

The AIPTW estimator for

(5)
$$\hat{E}[Y_{1}(a)]=\frac{1}{n}\sum_{i=1}^{n}\left\{\frac{I(A_{i}=a)Y_{1i}}{\hat{P}(A_{i}=a|C_{i})}-\frac{I(A_{i}=a_{i})-\hat{P}(A_{i}=a|C_{i})}{\hat{P}(A_{i}=a|C_{i})}\hat{E}(Y_{1i}|A_{i}=a,C_{i})\right\}$$

where $\hat{P}(A_{i}=a_{i}|C_{i})$ can be obtained using predictions from the propensity score model. The estimator in equation 5 can be used to estimate $E\left[Y_{1}\left(0\right)\right]$ and $E[Y_{1}(1)],$ and the difference between these two expectations is an estimate of the average treatment effect in the population. Standard errors can be obtained based on the efficient influence function.^28^

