##### Additional analysis in the UK Emulated Trial making use of data on treatment prescription dates

A limitation of this approach is that it assumes individuals with A=1 at time 1 have been taking azithromycin for the past 12 months. Realistically, individuals may initiate treatment with azithromycin at any time between time 0 and time 1. For the most recent time period, we can conduct a second analysis using the UK data and making use of data on treatment prescription dates.

In this second analysis, AIPTW is used as above, but the outcome model used previously (equation 3) is modified to include a variable indicating time and an interaction term between time and treatment. We define a new time variable, $t^{*}$, which measures time in months. For treated individuals, $t^{*}=0$ on the first date they are prescribed azithromycin after the index visit. For control individuals, $t^{*}=0$ for the date of the index visit. We let $Y_{t^{*}=12}$ denote FEV_1_% measured on the day of the annual review after $t^{*}=0$ and closest in time to $t^{*}=12.$ Note that this accommodates the fact that annual review visits do not always take place exactly 12 months apart. The outcome model will then be defined as:

(6)
$$Y_{t^{*}=12}=\delta_{0}+\delta_{A}A+\gamma_{c}C+\delta_{t^{*}}t^{*}+\delta_{At^{*}}At^{*}+\epsilon$$

After fitting this model, we set $t^{*}=12$ to obtain the relevant expected outcomes.

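### UK annual-review analysis: treatment is read at the follow-up visit but only time-0 covariates are adjusted for, so starts prompted by later deterioration bias the estimate against azithromycin

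*Protocol article*

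**What the plan says.** The relevant rules are in the protocol article, mostly under UK CF Registry Data (annual review data only).

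- Time 0 is the first eligible annual review. The treated label comes later: "Individuals are included in the treated group if they are recorded as being prescribed azithromycin at the follow-up visit". Likewise, "Individuals not recorded as being prescribed azithromycin at the follow-up visit are included in the control group". The reason given is that the annual review records treatment over the preceding year.
- "The outcome is FEV_1_% measured on the day of the follow-up visit", and that visit "falls within 9–15 months after time 0".
- Table 2 excludes people with "Prescription of chronic oral or prophylactic oral macrolides (including azithromycin) recorded at time 0". UK treated people are therefore those whose azithromycin is first recorded at the next review.
- Main analysis: the propensity score is "the probability of treatment conditional on baseline covariates", and the outcome model uses the same covariate set C.
- The Figure 2 legend describes the "association between azithromycin at time 0 (azithromycin0) and FEV1% at time 1 (FEV1%1").
- The section on the additional prescription-dates analysis concedes the timing problem: "Realistically, individuals may initiate treatment with azithromycin at any time between time 0 and time 1". Data availability, under Limitations, repeats it. Both present it as uncertainty about how long people were exposed. The response is one additional analysis, for UK 2016–2018 only.

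**The concern.** The label is settled by what happens between time 0 and the outcome, while the adjustment stops at time 0. The Covariates section says that prescribing follows clinical indication as well as preference. It lists intravenous days, hospital admissions, infections and rate of FEV1% decline as drivers of both prescribing and outcome. Those drivers can keep acting after the index review. A fall in lung function some months in can prompt a start and also lower FEV1% at month 12, and a covariate measured at time 0 does not record that new fall.

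This differs from the limitation the protocol names. Shorter exposure dilutes a benefit towards zero. Confounding by later deterioration pushes the estimate down and can make a null effect look like harm.

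The study's purpose is to judge replication by direction and significance, by whether the estimate lies in the trial's confidence interval, and by a standardised difference. Samples are expected to be much larger than the target trial's 82, so a biased UK estimate could also be a precise one.

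**Working it through.** The protocol has no figure to reproduce here. The check has two parts.

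**1. The text.** For the UK main analysis:

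| Element | Where it sits in time |
|---|---|
| Eligibility, covariates C | index review (time 0) |
| Azithromycin start | any time from index to follow-up review |
| Treatment label A | follow-up review (9–15 months) |
| Outcome | follow-up review, same day |

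The estimator needs A to be independent of the potential outcomes given C at time 0. If a start depends on deterioration S after time 0, and S also affects the outcome, S is a common cause of A and the outcome that lies outside C. Double robustness does not help, because both models omit S. E-values describe how strong an omitted factor would need to be; they do not correct the alignment.

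The dates-based analysis does not clearly remove the problem. It moves time 0 to the first prescription date for treated people but not for controls, and it describes no updating of C to that date.

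**2. Illustrative size.** Every input below is an assumption; none comes from the protocol. The simulation used 400,000 people per scenario.

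- Baseline F ~ N(85, 18²); post-index deterioration S ~ N(0, 1).
- Start at index: logit = −2.5 − 0.02(F − 85).
- Otherwise start mid-year: logit = −2.5 − 0.02(F − 85) + ln(OR)·S.
- A = 1 for either kind of start.
- Outcome = F − 2 − ρ·SD·S + effect × (1 if early, 0.5 if late) + N(0, 6²), with SD 4 or 8 and ρ 0.5 or 0.8.
- Analysis: the AIPTW estimator of equation 5, adjusting for F.

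| OR of starting per SD of deterioration | Estimate, true effect 0 | Estimate, true effect +3 |
|---|---|---|
| 1 | −0.02 to 0.03 | 2.23 to 2.29 |
| 1.5 | −0.53 to −1.34 | 1.78 to 0.90 |
| 2 | −0.78 to −2.36 | 1.49 to −0.16 |
| 3 | −1.18 to −3.85 | 0.91 to −1.78 |

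Hand check of the two components:

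- Dilution at OR 1, where 48% of the treated start late: 3 × (1 − 0.48 × 0.5) = 2.28, as simulated.
- Confounding at OR 2, SD 4, ρ 0.8, where 52% start late: if starts are uncommon, the mean of S among late starters is roughly ln(2) = 0.69. The bias is then about −0.52 × 0.8 × 4 × 0.69 = −1.15, against −1.22 simulated.
- Both together, true effect +3, same scenario: 3 × (1 − 0.52 × 0.5) − 1.22 = 1.00, as simulated.

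Aligned alternatives in the same data, treatment read at time 0:

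- Later starters censored with inverse-probability-of-censoring weights using S: −0.08 to 0.13 (true 0) and 2.92 to 3.06 (true +3).
- Later starters censored without weights: down to −0.62 (true 0) and 2.26 (true +3).

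**Sensitivity to start timing.** A different null model was also run: a monthly FEV1% random walk, with the log-odds of starting rising 0.05, 0.10 or 0.15 per point lost since index, adjusted for index FEV1%. Three codings gave −0.73/−1.43/−2.15, −0.78/−1.65/−2.47 and about −1.2/−2.5/−3.8. In the third, placing 75% of starts at the index review reduced the bias to −0.3/−0.8/−1.4, and placing 90% there reduced it to −0.2/−0.3/−0.6. In this model a 3-month grace-period design left −0.1 to −0.4.

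**The case against.** The choice is forced by the data and explained. Prescription dates exist only from 2016. Before that, the follow-up record is the only one covering the interval after the index review, and an index record of azithromycin leads to exclusion. The uncertain start date is disclosed and listed among reasons why results may differ from the target trial. All of that stands, but it explains the design without removing the bias, and the disclosure concerns duration alone.

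A reader might infer that conditional exchangeability must fail in all three UK periods. The document does not support that. Starts decided at or soon after the index review depend on index status, which C describes well: FEV1%, its recent change, intravenous days, admissions, infections and BMI. No start timing or trigger rate is given. Failure is a matter of degree.

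A reader might also infer a known size, or a reversal of sign. The simulations adjust for index FEV1% alone and make later deterioration independent of baseline, so no baseline covariate could have helped. Codings of the same broad model also disagree. Reversal appears in some scenarios, but the article does not state the target trial's effect size, so there is no benchmark.

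Finally, the azithromycin-at-time-0 label in Figure 2 might be read as a contradiction. The figures are not shown, and the article says that the source visit differs by registry. The label may mean treatment over the interval, extracted from a later visit. The point does not depend on it.

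**Conclusion.** The concern holds in conditional form. Follow-up assignment combined with baseline-only adjustment leaves confounding by indication after the index review uncontrolled, and the protocol does not name it. That starts respond to deterioration is an inference from the Covariates section; it is plausible but not quantified there. Given that it happens, the bias runs against azithromycin: this was the direction in every simulated scenario with an odds ratio above 1.

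The size cannot be derived from the document. Illustrative null results run from near zero, when starts are unrelated to deterioration, through a few tenths of a point when 90% of starts occur at the index review, to nearly 4 FEV1% points under strong triggering.

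It would go too far to conclude that 2003–2005 and 2007–2009 must leave the replication assessment. The Time periods section chose 2003–2005 as closest to the target trial, so closeness in calendar time has to be weighed against this bias.

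**What to change.** 1. For 2016–2018, define the dates-based analysis with time 0 at the index review in both groups. Treated status is a start within a short, prespecified grace period. Censor later starters with inverse-probability-of-censoring weights that use the post-index data available, or use clone-censor-weight. Make this the lead UK estimate for that period.
2. Run the annual-review-only method on the same 2016–2018 patients and report the difference between the two estimates as an indication of its bias.
3. Keep 2003–2005 and 2007–2009. Label them as open to post-index confounding by indication, state the expected direction (against azithromycin) in the analysis and limitations sections, and interpret their replication criteria in that light.

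The cost is modest extra analysis and some rewording, with no new data. There will be fewer treated people, because late starters no longer count as treated, and some bias will remain within the grace period. The weights can be only as good as the data between reviews. The article describes dated intravenous antibiotic treatment but, for the UK, clinical measurements at roughly annual reviews. The difference in step 2 also includes dilution from late starts, so it indicates the confounding without isolating it.

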### Data availability

The target trial specified a particular dose of azithromycin depending on an individual’s weight. The trial also reported high adherence, estimated at 95% for azithromycin and placebo. Neither the UK nor US Registry provides reliable data on treatment doses, and it is possible that individuals in the registry will take different doses to those given in the target trial (see table 2). There are also no data on adherence, and our emulated trial relies on data on treatment prescription, which may differ from actual treatment use.

Some of the exclusion criteria of the target trial cannot be replicated exactly in the emulated trial. For example, the target trial included a criterion based on liver function tests, with individuals excluded if they had liver disease with liver function tests more than twice the laboratory upper limit. In the UK Registry, the closest variable to this criterion is an indicator for acute liver failure with liver function tests greater than three times the laboratory upper limit. The US Registry has a similar variable, but data collection for this variable began in 2015, so it can only be used for the most recent time period.

The target trial calculated the outcome, FEV_1_%, using the Knudson equations^31^; we plan to use the GLI equations in the emulated trial,^25^ as these are now more commonly used. Previous research suggests that results will be minimally affected by choice of reference equations.^32^

The main analyses in the UK emulated trials will use data from consecutive annual review visits. We assume that the annual review visits are 12 months apart and that individuals in the treatment group were taking azithromycin for the 12 months in between visits. In practice, the annual review visits are not always exactly 1 year apart, and individuals may begin treatment with azithromycin at any time during the time between visits. We address this limitation to some extent in an additional analysis for the UK Registry data, in which we incorporate prescription date data.

Finally, our analysis relies on the assumption that all confounding of the treatment-outcome association is accounted for in the analysis. It is possible that there are some factors associated with both azithromycin prescription and the outcome that are not collected in the registry. We plan a sensitivity analysis to assess how sensitive our results are to unmeasured confounders.

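### UK prescription-date analysis: the clock starts at first prescription for the treated but at the index review for controls, the gap is not adjusted for, and the 9–15-month window drops mid-interval starters

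*Protocol article*

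**What the plan says.** - **Definition of time 0 and the index visit**: the index visit is where eligibility is met, "such that the date of the index visit is time 0".
- **UK CF Registry Data, prescription-dates paragraph**: for the treated, "time 0 is defined as the first date post-index visit at which azithromycin is prescribed"; controls keep the index visit. "The follow-up visit is defined as the next annual review visit which is closest to 12 months after time 0", and it must lie 9–15 months after time 0.
- **Additional analysis in the UK Emulated Trial**: "For control individuals, $t^{*}=0$ for the date of the index visit". The outcome is taken at the review nearest to t*=12, without repeating the window, and the text adds: "Note that this accommodates the fact that annual review visits do not always take place exactly 12 months apart". Model (6) adds t* and its interaction with treatment; t* is then set to 12 "to obtain the relevant expected outcomes". The estimator is otherwise the AIPTW of equation 5.
- **Table 2**: excludes people with a macrolide prescription recorded at time 0, and people without a follow-up visit for time 1.
- **Covariates**: rate of decline in FEV1% is taken from the index visit and the visit before it. Covariate timing in general is referred to Figure 1, which is not shown in the text available.
- **Limitations, Data availability**: "We assume that the annual review visits are 12 months apart". The dates analysis is presented as a partial remedy only.

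**The concern.** The dates analysis was added because the main UK analysis treats everyone recorded on azithromycin at follow-up as having had 12 months of it. Moving time 0 to the prescription date for one arm addresses that, but it separates eligibility, covariate measurement and start of follow-up in the treated while leaving them together in controls. Three consequences follow.

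1. Lung function declines between index review and prescription in the treated. Nothing in model (6) represents that interval, so the decline is attributed to azithromycin.
2. Whether a treated person has a usable outcome review depends on the month in which treatment began. Controls face almost no such restriction.
3. With time 0 moved to the prescription date, Table 2's macrolide exclusion, read literally, removes every treated person.

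This is the only analysis offered against the UK timing limitation, so a distortion here would undermine the comparison it is meant to support.

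**Working it through.** The plan states no figure for these losses or gaps, so there is none to reproduce.

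**Inputs from the protocol.** Reviews 12 months apart (Limitations, Data availability); window 9–15 months after time 0 (UK CF Registry Data); initiation at any time between reviews, with no distribution (Additional analysis). **Assumed here:** the distribution of start months, a review-gap SD of 0–2 months, and a decline of 1–3 FEV1% points a year.

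**1. The window.** If treatment starts s months after the index review, the next two reviews fall 12−s and 24−s months after time 0.
- 9 ≤ 12−s ≤ 15 requires s ≤ 3.
- 9 ≤ 24−s ≤ 15 requires s ≥ 9.

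Starts with 3 < s < 9 have no qualifying review. If starts are even over the year the loss is 6/12 = 50%. Controls have s = 0 and a review at 12 months, so none are lost. In a simulation of 400,000 starts with review-gap SD of 1–2 months, 50–51% of the treated and 0.3–13% of controls were lost. Other start patterns give:

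| Start pattern | Treated lost | Mean months, index review to outcome (retained) |
|---|---|---|
| Even, exact 12-month spacing | 50% | 18.0 |
| 25% within a month of index, rest even | 38% | 15.6 |
| 50% within a month of index, rest even | 26% | 14.0 |
| 75% within a month of index, rest even | 13% | 12.9 |
| Clustered mid-interval, beta(2,2) | 67% | 18.1 |
| Weighted to late in the interval, beta(2,1) | 50% | 22.2 |
| Even, exact spacing, very next review only | 75% | 12.0 |

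Rows 2–6 use a review-gap SD of 1 month.

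**2. The gap.** Under even starts, half of the retained treated (s ≤ 3) have their outcome 12 months after index and half (s ≥ 9) at 24 months: (12 + 24)/2 = 18. Without the window, starts before month 6 use the 12-month review and later ones the 24-month review, so the mean is again 18. Controls have 12. The excess is 6 months: 6/12 × 1 = 0.5 and 6/12 × 3 = 1.5 points lower in the treated, a bias against azithromycin. Setting t*=12 does not remove it. Mean t* among the retained is (10.5 + 13.5)/2 = 12, so the prediction at t*=12 describes people who are on average 18 months past the index review.

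**3. Calendar.** Recruitment covers 2016–2017. A start with s ≥ 9 needs the review 24 months after index, which falls inside 2018 only if the index date is in the first 12 of the 24 recruitment months. With even index dates, retention is 25% + 25% × 12/24 = 37.5%, a loss of 62.5% if 2019 reviews do not count.

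**4. Equation 5.** With the indicator read as I(A_i=a), equation 5 is the mean of m + I(A=a)/P × (Y − m), where m is the outcome prediction. If m is set at t*=12 in both places while Y was observed at the actual t*, the weighted residual adds back slope × (mean t* − 12). The estimate then reverts to the arm's mean t*. Under even starts mean t* is 12 and the error is zero. If only the very next review counts, within the window, mean t* is 10.5; with an illustrative slope of −2 points a year the error is (−2/12) × (10.5 − 12) = +0.25 points. As printed, the second indicator is I(A_i=a_i), which always equals 1.

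**The case against.** The separate origin is deliberate: the paragraph distinguishes index visit from time 0, and t* counts from treatment start as intended. The protocol claims only partial relief, and this is one supplementary analysis in one registry and one period. These points stand, and they limit the severity.

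A reader might infer more than the documents support:

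- **That half the treated will be lost.** This needs even starts, and the protocol gives no distribution.
- **That a 75% loss and an 18-month gap occur together.** They need incompatible readings of which annual review counts as the next. On the reading that gives 75%, the gap disappears.
- **That the analysis fails to repair the timing problem.** Retained treated people do have 9–15 months since first prescription, so time on drug is corrected for them.
- **That the two sections contradict each other on the window.** The Additional analysis section merely does not restate it. That is an omission, though it leaves two analysts free to build different samples.
- **That the lost starters make the result biased.** Loss depends on start month, but nothing shows that start month is related to prognosis. The certain cost is precision.
- **That the time correction is certainly cancelled.** The text does not say at which t* the residuals are evaluated, and the error is zero when mean t* is 12.
- **That covariates certainly date from the index review.** The text fixes this only for rate of decline, and Figure 1 may settle the rest. It is likely for FEV1%, since the UK registry collects its longitudinal clinical measurements at annual reviews.

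None of this answers the core: the origins differ by arm, and model (6) has no term for the gap.

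**Conclusion.** The point holds in limited form and should be corrected before this analysis is run; it is not critical. The plan corrects time on drug for retained treated people but adds a misalignment between arms and a loss that depends on start month. The bias of −0.5 to −1.5 FEV1% points rests on index-review covariates, even starts, use of the closest review, and an assumed decline of 1–3 points a year. It is smaller if starts cluster soon after the index review, larger if they come late in the interval, and absent if only the very next review counts. The size of the loss likewise depends on start pattern and reading. The literal conflict between Table 2's macrolide exclusion and the moved time 0 depends on no assumption and must be reconciled. The main UK and US analyses are unaffected.

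**What to change.** (a) Assess eligibility at the index visit in this analysis and use one origin for both arms. For example, give each control a pseudo-start drawn from the treated distribution of index-to-prescription lags, choose the control's outcome review relative to it, confirm control status up to that review, and add months since index review to C. Adding the gap without pseudo-starts does not work: it is zero for every control and so identifies the arm. Sequential trials from each index review are an optional alternative, but a larger redesign.

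(b) State one follow-up rule in both sections. The review closest to t*=12 without the 9–15-month exclusion is preferable, because model (6) already carries t*. Under even starts this keeps the mid-interval starters, with follow-up then spanning 6 to 18 months.

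(c) Print I(A_i=a) in equation 5. For this analysis compute the mean of m(a,C,12) + I(A=a)/P × [Y − m(a,C,observed t*)]. Also correct the cross-reference that calls equation 3 the outcome model; that is equation 4.

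(d) State whether 2019 reviews count. Admitting them retains late starters recruited in 2017, but runs against the protocol's reason for ending in 2018, namely to predate widespread CFTR modulator use.

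The cost is wording and code, bootstrap or robust standard errors to reflect the drawn pseudo-starts, and a wider spread of follow-up times that leans more on the linear time term.
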